### Eligibility Criteria

The mental health consumers who will be invited to participate are all existing consumers of an ACT Health community-based mental health service in Canberra, Australia. All consumers who have given informed consent will be eligible to participate in the study. Intended staff participants are the peer worker conducting the e-mental health program, the peer supervisor, and other staff of the mental health service.

### Recruitment

The e-mental health program will be delivered in 4 sessions to attendees at drop-in clinics during their usual appointments at the mental health service. It is anticipated that the program will be delivered over a period of approximately 4 months, commencing June 2017.

Recruitment into the e-mental health program will be conducted by staff at the mental health service. Attendees at drop-in clinics will be offered the opportunity to take part in a peer worker-led recovery program during their appointments at the clinic. This is partly to assess the utility of the app during a time in which the consumers must be present at the clinic to receive medication. The program will consist of completing the Stay Strong recovery app on iPads with the support of the peer worker over approximately 4 sessions. We initially conceptualized the peer worker to lead a group session for the app; however, group delivery is not feasible in the drop-in clinic setting, where consumers arrive and depart at varying times.

### Research Study

#### Evaluation Survey

After completion of the e-mental health recovery program, the consumer researchers will invite those who took part to participate in the evaluation survey. Participation will involve completion of a short questionnaire about experiences with the peer worker and the e-mental health program. We will also offer consumers the opportunity to take part in a focus group discussion to evaluate the program in more depth with researchers and each other. Participation in the recovery program and in the research for consumers will be handled separately—consumers will be offered the opportunity to take part in the program by the peer worker as part of their usual contact with the mental health service. The researchers will recruit consumers for the evaluation and it will be made clear to consumers that participation in the evaluation is completely voluntary and independent of their participation in the recovery program or the services they receive at the mental health service. Potential participants will also be informed that staff will not see their individual answers to minimize the chance of social desirability responses. The recruitment target for the research is 30 consumers across 3 clinics. Staff of the mental health service predicted this is a feasible target based on current attendance at the service.

#### Focus Groups

We will recruit up to 10 consumers who complete the questionnaire to participate in the focus group discussion(s). The focus group(s) will be described during the administration of the questionnaire. We will collect details for consumers who are interested in participating in the focus group and will follow-up with these consumers to schedule the focus group(s).

#### Staff Interviews

In addition to the consumers of the mental health service, staff involved in the trial of the peer worker-led e-mental health program will also be invited to participate in an interview. The peer worker will be interviewed about their experience of the delivery of the app. Supervisory and management staff at the service will not be involved in the delivery of the app, but will be asked to participate in one-on-one interviews to discuss their observations of the feasibility of embedding a peer worker and e-mental health program within the service from an operational point of view.

The evaluation materials for the survey, focus groups, and interview are presented in Multimedia Appendix 3.

### Outcomes

#### Consumer Questionnaire

We will measure the participants’ perception of their own recovery using the Self-Identified Stages of Recovery (SISR) measure [24]. The SISR is a single-item scale describing stages of recovery and the participants’ perception of the stage of recovery with which they currently identify. Participants are asked to indicate which of 5 statements most closely describes how they have been feeling over the past month, with higher ratings indicating more positive perceptions of recovery. Examples of statements are:

I don’t think people can recover from mental illness. I feel that my life is out of my control, and there is nothing I can do to help myself.Question 1

I feel I am in control of my health and my life now. I am doing very well and the future looks brightQuestion 5

The single-item of the SISR has been argued to measure a unique aspect of recovery not assessed by continuous measures [25]. In addition, the single-item SISR has demonstrated reliability and concurrent validity [26] as well as convergent validity for the staged model of recovery [25].

Seven questions designed by consumer researchers will subsequently ask participants to rate their experience with the peer worker and the program on a 4-point scale from “Not at all” to “Yes definitely.” The questions were designed to explore the acceptability of a peer worker and an e-mental health program as a part of the service, as well as investigate recovery and self-efficacy. There is an open-ended section for any further remarks. The questionnaire will be conducted at the conclusion of the final session of the program delivery, within the usual time that consumers are attending the clinic for treatment.

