### Aims

The aim of this project are to determine if a peer worker-led e-mental health recovery intervention is a feasible, acceptable, and effective adjunct to usual treatment for people with moderate to severe mental illness, as determined by the type of diagnosis, duration and/or intensity of symptoms and degree of functional impairment [16]. As an exploratory proof-of-concept study, the primary focus will be on elements of the program that consumers find useful or not useful, barriers and facilitators to implementation from the peer worker and service perspective, and primarily qualitative investigations of effectiveness for recovery outcomes. The findings of the research will help inform a larger investigation of the role of peer workers and e-mental health, which can guide the future implementation of these initiatives within existing mental health services.

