### Objectives

The primary objectives of the study are (1) to investigate the feasibility and acceptability of embedding a peer worker in a public mental health service, from both the consumer and service perspectives; and (2) to assess the acceptability and effectiveness of a recovery-focused e-mental health program as an adjunct to treatment as usual for people with moderate to severe mental illness.

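### The questionnaire is offered only on finishing the program, and the focus group only to questionnaire completers, so consumers who stop early have no stated route to give their views

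*Protocol article*

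**What the plan says.** Three sections of the protocol article settle which consumers are heard.

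- **Evaluation Survey:** "After completion of the e-mental health recovery program, the consumer researchers will invite those who took part to participate in the evaluation survey".
- **Consumer Questionnaire (Outcomes):** "The questionnaire will be conducted at the conclusion of the final session of the program delivery", during usual clinic time.
- **Focus Groups:** up to 10 members, recruited from consumers who have completed the questionnaire. The Outcomes section allows interviews instead if too few can be found for a group.

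The Recruitment section describes the program as completing the app "with the support of the peer worker over approximately 4 sessions". The evaluation target is 30 consumers across 3 clinics.

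On purpose, the Aims say that "the primary focus will be on elements of the program that consumers find useful or not useful". The second primary objective is "to assess the acceptability and effectiveness of a recovery-focused e-mental health program as an adjunct to treatment as usual". The Analysis Strategy plans descriptive statistics, including mean scores on the Self-Identified Stages of Recovery (SISR) item and a mean for each experience question, the latter rated on a 4-point scale.

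**The concern.** A consumer who stops after one, two or three sessions does not complete the program. The stated invitation does not reach that person, and neither does the focus group, because entry depends on the questionnaire. Both consumer sources therefore condition on completion, which is plausibly related to how acceptable the program was. People who stopped early are an important source on what was not useful.

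The Introduction itself names low uptake and completion as a known difficulty of e-mental health and suggests that peer support might help. The Limitations section covers the single peer worker and the difficulty of separating peer worker from app, but not this selection. Recruiting more consumers under the same rule would narrow the sampling error and leave the selection unchanged.

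**Working it through.** **Does any stated route reach an early stopper?**

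1. The survey invitation refers to those who took part, which could be read broadly, but the same sentence places it after completion. The Consumer Questionnaire section repeats that timing.
2. The final session has to mean each consumer's own last program session, because the Outcomes section spreads questionnaires over about 4 months.
3. An early stopper's last session is usually recognised as the last only afterwards, so a researcher cannot administer the questionnaire at its close. Data Collection limits each participant to one research occasion apart from the focus group, so the questionnaire is not repeated at each session.
4. The focus group, or the interview that may replace it, depends on step 1.
5. Staff and peer worker interviews remain, but they give only a second-hand view of why consumers stopped.

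The text shown contains no other route.

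**How much could it matter?** The plan has no figure to reproduce. The target of 30 is justified by a staff prediction from attendance, and no completion rate is stated. What follows is illustration on the plan's own scale, a mean 4-point rating.

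Inputs, all assumed: options scored 1 to 4; completer mean 3.4; early-stopper mean 1.5, 2.0 or 2.5; completion proportion c from 0.9 to 0.4.

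Mean for all starters = c × 3.4 + (1 − c) × m, where m is the early-stopper mean.
Overstatement = 3.4 − that mean = (1 − c) × (3.4 − m).

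| c | all starters, m = 1.5 / 2.0 / 2.5 | overstatement |
|---|---|---|
| 0.9 | 3.21 / 3.26 / 3.31 | 0.19 / 0.14 / 0.09 |
| 0.8 | 3.02 / 3.12 / 3.22 | 0.38 / 0.28 / 0.18 |
| 0.6 | 2.64 / 2.84 / 3.04 | 0.76 / 0.56 / 0.36 |
| 0.4 | 2.26 / 2.56 / 2.86 | 1.14 / 0.84 / 0.54 |

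Worked line: c = 0.6, m = 2.0 gives 0.6 × 3.4 + 0.4 × 2.0 = 2.84, and 3.4 − 2.84 = 0.56.

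If nothing is assumed about early stoppers, m can lie anywhere from 1 to 4. At c = 0.8 the all-starter mean then lies between 0.8 × 3.4 + 0.2 × 1 = 2.92 and 0.8 × 3.4 + 0.2 × 4 = 3.52. At c = 0.6 it lies between 2.44 and 3.64. The upper ends exceed 3.4, so the completer mean could also be too low.

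**Effect on numbers.** Reaching 30 completers needs 30 / c starters: 34, 38, 50 or 75 at c = 0.9, 0.8, 0.6 or 0.4, before any refusal of the voluntary survey.

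**The case against.** The strongest reply is that the article never excludes early stoppers. It opens eligibility to all consenting consumers, fixes a time for the questionnaire, and is silent on stopping early. The recruitment flowchart and the evaluation materials are not shown and may deal with it. This stands as a caution about wording: the defect is the absence of a stated route, not an exclusion clause. It does not remove the point, because a flowchart that invited early stoppers would conflict with the timing given in the text.

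Second, sessions take place while consumers attend to receive medication, so finishing may partly reflect attendance rather than liking the program. This also stands. It weakens any claim about the size of the bias and leaves its direction likely rather than certain.

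Third, the study is an exploratory, descriptive and largely qualitative proof of concept. Completers can say what they disliked, the questionnaire has an open-ended section, and staff are asked about challenges. So the aim is limited rather than defeated, and completers' views remain usable if labelled as such.

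A reader might infer three stronger points that the article does not support:

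- That the peer worker decides who has had a final session. Nothing says so: researchers issue the evaluation invitation and collect all data, and an approximate session count is ordinary flexibility in a drop-in clinic.
- That SISR scores must be biased upward. SISR records self-identified recovery stage over the past month, not satisfaction, and the article does not link it to completion in either direction.
- That an inflated percentage finding the program acceptable will be reported. The article defines no such percentage or threshold.

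**Conclusion.** The concern holds in a limited form. Under the stated timing, acceptability ratings and views on what was not useful would come from completers only, although acceptability is a primary objective. The experience ratings are likely, but not certain, to be too favourable for everyone who started. The bias is zero if everyone completes or if early stoppers would answer as completers do.

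Its size cannot be derived from the article. The illustrated 0.09 to 1.14 points on a 4-point scale follow entirely from the assumed completion of 90% to 40% and the assumed means. The direction for SISR is unclear. This is a sampling rule that the article states, not detail left to a fuller document, and a better rule is available.

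**What to change.** Amend Evaluation Survey, Focus Groups and Consumer Questionnaire so that every consumer who starts at least one session is invited to the questionnaire. The invitation would come at the final session or, for those who stop early, at a later clinic attendance. Open the focus group or interview to the same people.

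In the Analysis Strategy, report how many started, completed, were invited and responded, and give ratings for all responding starters. Describe completers and early stoppers separately only where numbers allow this without identifying anyone. With 30 starters and 80% completion there would be about 6 early stoppers before refusals (30 × 0.2), and the study already forgoes demographic data to protect identity.

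If early stoppers cannot be reached, label the results as completers' views and add this to the Limitations.

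**Cost:** changes of wording and probably a small ethics amendment. The service also needs a way to pass the invitation to early stoppers while keeping program and evaluation recruitment separate, as Evaluation Survey and Ethical Issues require. Some will refuse, and headline ratings may fall. The setting helps: consumers come for medication, researchers already collect data at the clinics, and interviews are already allowed as a fallback.

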#### Focus Group

The focus group will follow a semi-structured protocol, investigating experiences with the Stay Strong program and its delivery. This will provide consumers with an opportunity to discuss and reflect on their experiences with the peer worker and the program in more detail than the rating scales allow. It will also enable identification of aspects of the program that consumers like and dislike to inform possible future delivery. The focus group method was selected to facilitate richer information where participants can share and build on each other’s ideas. However, we will consider an interview method if we cannot secure sufficient participants for a focus group. The focus group will also be scheduled during usual clinic hours in a meeting room at a mental health service clinic.

The focus group will be facilitated by one researcher with a second researcher as note taker/assistant. The group will be audio-recorded and participants will be advised in the information sheet and accompanying explanation that this is necessary to avoid missing anything and they should decline to participate if not comfortable with recording. They will also be advised that if they choose to withdraw during the focus group—it will not be possible to delete their contributions to that point.

#### Staff Interviews

Interviews will also follow a semi-structured protocol. The peer worker and other staff associated with the implementation of the program (eg, peer supervisor, health service coordinator) will be asked to discuss the benefits and challenges of the program, their experiences with both the peer worker model and the e-mental health program, and issues that may need to be considered for future delivery. Interviews with staff will be scheduled at a time and location convenient for the staff member. Interview participants will be asked if they consent to recording; if they refuse, the researcher will rely on written notes (Figure 1).

Questionnaires with consumers will be conducted across a period of approximately 4 months. The focus group and staff interviews will be conducted at the conclusion of the program. Data analysis and write-up is planned for completion by December 2017.

**Figure 1 figure1:**
[figure not shown]
Recruitment flowchart.

### Data Collection

All data collection will be conducted by members of the research team who will discuss protocols prior to commencing data collection to ensure consistency. Each participant will only be required to take part in the research on one occasion, with the exception of consumers who also choose to take part in the focus group. Due to the small sample and study location, no demographic data will be collected to minimize the chance of identifying individuals. All participants in the qualitative data collection will be advised that while every effort will be made to remove identifying information, they may still be identifiable from their comments.

### Data Management

All data will be stored securely in locked offices at The Australian National University (ANU). Consent forms and written questionnaires will be kept separately in locked filing cabinets. Digital data, including audio recordings, transcripts, and analysis files will be kept on password-protected computers at the ANU, accessible only to the research team. Identifying information will be removed from interview and focus group data during transcription and this will be reviewed by a member of the research team. Interview participants will have the opportunity to review their transcripts for accuracy and to identify any comments they do not wish to have included in publications. Data will be stored for a period of 5 years from last publication, after which it will be deleted and paper records destroyed.

### Analysis Strategy

Quantitative analyses of questionnaire responses will comprise descriptive statistics and will be conducted in SPSS (IBM) by 1 member of the research team. These will include mean SISR scores and mean ratings on each of the experience questions. Qualitative analyses of the focus group and interview transcripts will be managed using NVivo qualitative analysis software (QSR International). A framework analysis approach [15], incorporating both inductive and deductive coding, will be used to identify the key issues raised by consumers and staff. Initial coding will be conducted by 1 member of the research team and the coding frame discussed with the rest of the research team before coding is finalized.

### Risks and Benefits

The primary risk to consumers is that working through a recovery-oriented mental health program and answering questions related to recovery may raise uncomfortable memories or feelings, and may exacerbate mental health problems. However, the presence of a peer worker to support people as they work on the program, together with the specific purpose and format of the Stay Strong program are designed to minimize these risks. The study is being conducted as an adjunct to treatment as usual for this group, ensuring ongoing monitoring by mental health professionals.

It is expected that the people with mental health problems who participate in the study will increase their understanding of the psychosocial factors that influence their mental health, may develop skills in self-advocacy and self-support, and will develop a better understanding of the tools and skills they have to help them manage their well-being. They may also experience a sense of shared experiences and belonging with the peer worker and feel empowered by the opportunity to contribute to evaluating services.

The staff involved in the research will experience a different, non-clinical way of providing services to their consumers that may inform their own recovery-oriented practice. The standardized use of peer workers and e-mental health recovery interventions has the potential to improve both the availability of services (increased workforce) and to enhance self-help and maintenance of well-being in clinical care. This proof-of-concept study will provide preliminary data on the feasibility and acceptability of this approach.

### Quality Assurance and Monitoring

The design and progress of the study will be discussed with the Consumer and Carer Advisory Group for ACACIA: The ACT Consumer and Carer Mental Health Research Unit. This group comprises representatives from the ACT Mental Health Consumer Network, Carers ACT, ACT Health and independent consumers and carers from the community. The role of the advisory group is to provide feedback and assistance on ACACIA research projects, such as suggesting improvements to design and materials and assisting with recruitment.

Regular email and face-to-face meetings between the research team and the ACT Health team managing the program will also occur to monitor the progress of the program and the implications for the research study.

### Ethical Issues

The mental health consumers who will be invited to participate are all existing consumers of the mental health service and the intended staff participants are all employees of ACT Health. To minimize the risks presented by these existing relationships, recruitment of consumers into the e-mental health program will be undertaken by staff of ACT Health, whereas recruitment of consumers into the evaluation will be undertaken by a member of the research team employed by The Australian National University (ie, not an ACT Health employee and not a person involved in treatment). The information sheet details the principles of voluntary consent and participation, including that there will be no adverse consequences of choosing not to participate. The researcher present during the questionnaires, focus group(s), and interviews will verbally confirm understanding of the voluntary nature of participation before collecting written consent to proceed. Consumers can take part in the peer worker-led program and not be required to take part in its evaluation. In addition, the principles of voluntary participation for staff will also be discussed with the potential staff participants to ensure staff and their managers understand their rights to refuse to participate or withdraw without consequence.

### Informed Consent

All participants will be provided with a participant information sheet when invited to take part in the study. The key aspects of the study and ethical considerations will also be described verbally and participants will have the opportunity to discuss the study with researchers before agreeing to participate. In particular, the researchers will ensure that both consumers and staff understand that they are not obliged to participate in the research, regardless of their participation in the program and there are no consequences for refusing to take part. All participants will complete a written consent form (Multimedia Appendix 4). Consumers who choose to participate in the focus group in addition to the questionnaire will receive an additional information sheet explaining the issues particular to a group discussion and will sign a separate consent form.

